## Abstract

**Background:**

In unipolar, and bipolar affective disorders, there is a high risk of relapse that increases as the number of episodes increases. Naturalistic follow-up studies suggest that the progressive development of the diseases is not prevented with the present treatment modalities. It is not known whether centralised and specialised secondary care intervention initiated early after the onset of the diseases can prevent the progression and thereby improve the prognosis.

**Methods:**

Two randomised clinical multi-centre trials comparing a centralised and specialised outpatient intervention program consisting of combined pharmacological and psychological intervention with standard decentralised psychiatric treatment. Patients discharged from their first, second, or third hospitalisation due to a manic episode or bipolar disorder (trial 1) or to a single depressive episode or recurrent depressive disorder (trial 2) were randomised. Central randomisations for both trials were stratified for the number of hospitalisations and treatment centre. The primary outcome measure for the two trials is time to re-hospitalisation with an affective episode.

**Discussion:**

These trials are the first to evaluate the effect of a centralised and specialised intervention in patients with early severe affective disorders. The trials used a pragmatic design comparing a specialised mood disorder clinic intervention with decentralised, non-specialised standard psychiatric treatment.

**Trial Registration:**

ClinicalTrials.gov: NCT00253071

## Background and objective

### Background

Affective disorders are associated with a high risk of relapse and the risk of relapse increases as the number of previous episodes increases [1,2]. Many patients do not recover to previous psychosocial function [3,4]. A proportion of patients present with cognitive impairment also during the remitted phase [5-7], and the risk of developing dementia seems increased in the long run [8,9]. It is well documented from randomised clinical trials that the risk of a new episode in bipolar disorder can be reduced significantly by treatment with lithium or other mood stabilizers [10]. In unipolar disorder continued treatment with antidepressants significantly reduces the risk of relapse [11]. Further, the prophylactic effect of medical treatment may be enhanced by psychoeducation or cognitive behavioural therapy in bipolar disorder [12-17] and by cognitive behavioural therapy in unipolar disorder [18-20]. However, results from naturalistic follow up studies suggest that the progressive development of the diseases is not prevented in clinical practice with the present treatments [21-23]. Part of the explanation may be decreased adherence with mood stabilizers and antidepressants, [24-29] but another explanations may be delayed intervention - pharmacologically and psychologically. Results from a number of studies comparing specialist first episode anti-psychosis programs versus standard treatment have shown that there are positive effects of early and sustained intervention following the first psychotic episode [30]. Within affective disorders, a number of studies have investigated the effect of health-service interventions in bipolar disorder [31-35] and recurrent depressive disorder [36-41]. However, to the best of our knowledge, no randomised clinical trial has investigated the effects of centralised and specialised combined pharmacological and psychological intervention in the early phases of unipolar or bipolar disorders. There are indirect suggestions that early intervention may improve the course and outcome in affective disorders. As summarised by Berk et al. [42], lithium for instance may be less effective in bipolar disorder as well as in unipolar disorder if not initiated early [43-45] although not all studies confirm this finding [46,47]. Further, response to cognitive behavioural therapy (CBT, [48]) and to psychoeducation [49] may be more effective when used during the early course of illnesses than after a dozen illness episodes, although a meta-analysis showed no clear evidence that the numbers of episodes moderate the effect of psychological therapy [50]. In addition, brain imaging data suggest that cognitive decline and reduction in brain volume are linked to recurrences [51] and cognitive dysfunction may increase with increasing numbers of episodes [52]. Finally, lithium and other mood stabilizers may have protective effects decreasing the tendency to cognitive decline [53-57] but existing data does not lead to any definite conclusion of a neuroprotective effect of long-term lithium therapy. Similarly, data do suggest that maintenance antidepressants prescribed for unipolar depressive disorder may have neuroprotective abilities but this is not definitive either [58,59].

It is likely that affective disorder patients are more able to benefit from medication, psychoeducation, cognitive behavioural therapy, or any other intervention if the intervention takes place early during the course of illness before a decline in psychosocial or cognitive function becomes manifest [42]. There are several difficulties in studying the effect of early intervention in affective disorders in general and bipolar disorder in specific [60]. The specificity of prodromal symptoms of the first episode is unknown and even when patients have had several episodes there is a delay of referral to treatment that prolongs time to accurate diagnosis and treatment [61]. In the present trials we focused on patients with severe affective disorders who were hospitalised for an affective episode. We only included patients after the first, second, or third time of hospitalisation. The present paper presents the background, hypotheses, design, outcomes, and statistical analyses of the two trials.

### Hypotheses

Based on the literature we hypothesised that centralised and specialised outpatient intervention of patients early in the course of severe affective disorder:

1) decreases the risk of re-admission to a psychiatric hospital;

2) decreases the risk of relapse of new affective episodes;

3) increases adherence with medical treatment;

4) increases quality of life; and

5) increases satisfaction with treatment

compared with decentralised, non-specialised psychiatric outpatient treatment.

### Objective

The aim of the present trials is to investigate whether centralised and specialised outpatient secondary care intervention for patients with severe affective disorder improve prognosis compared with standard psychiatric outpatient treatment in patients early in the course of mania/bipolar disorder (trial I) or depression/recurrent depressive disorder (trial II). The trials are naturalistic with very few exclusion criteria and investigate the effect among patients following psychiatric hospitalisation in The Capital Region of Denmark. When hospitalised patients were diagnosed and treated by the clinicians employed at the hospital. This pragmatic design was chosen to obtain a high generalisability of results from the trials to clinical settings regarding patients with the most severe affective disorders [62].

## Methods

### Study design

Patients were included from seven out of the nine psychiatric wards in The Capital Region of Denmark.

### Participants and screening

According to the sample size calculation, it was planned to randomise a total of 180 patients with a manic episode/bipolar disorder (trial I) and 260 patients with a single depressive episode/recurrent depressive disorder (trial II) to outpatient intervention in a centralised and specialised mood disorder clinic versus standard outpatient treatment. Patients in the experimental group were offered intervention in the mood disorder clinic consisting of a combination of psychopharmacological and psychological intervention and social intervention.

### Randomisation

Patients were randomised to the intervention group or the control group at the end of the index hospitalisation. Randomisation was conducted centrally by the Copenhagen Trial Unit according to a computer generated allocation sequence to secure allocation concealment. In this way randomisation was independent of the professionals delivering treatment. The ratio of randomisation between the intervention and the control group was 1:1. Randomisation was stratified according to two variables: 1) psychiatric centres and 2) number of previous psychiatric hospitalisations (0, 1, or 2). The randomisations were carried out with varying block sizes unknown to the site investigators.

### Inclusion and exclusion criteria

Inclusion criteria: Patients discharged from their first, second or third hospitalisation from a psychiatric ward with an ICD-10 diagnosis of a manic episode or bipolar disorder (ICD-10 code: DF30-31.9) or a single moderate or severe depressive episode or recurrent depressive disorder (ICD-10 code: DF32.1-33.9) as the primary diagnosis. Comorbidity with alcohol or substance abuse and other psychiatric disorders were allowed. The patients were diagnosed by the medical doctor at the local psychiatric ward. Age was between 18 and 70 year old. The patients were able and willing to give written and oral informed content.

Exclusion criteria: Patients with moderate or severe dementia. Patients with poor understanding of Danish language. Patients under any kind of psychiatric involuntary commitment.

### Blinding

Blinding of patients and the treating clinicians was not possible as patients were randomised to the mood disorder clinic or to standard treatment. Nevertheless, statistical analyses and the writing of the scientific paper including introduction and results will be carried out before data are unblinded.

### The mood disorder clinic

Patients in the intervention group were treated in a specialised outpatient mood disorder clinic at Psychiatric Centre Copenhagen, Rigshospitalet, Copenhagen University Hospital. The clinic was established September 2004 in parallel to the work and publication of a Health Technology Assessment (HTA) report on outpatient treatment in severe affective disorders [63], chaired by the last ([name]) and first author ([name])). The HTA report examined the following three key aspects of outpatient treatment of patients with major affective disorder:

• Prophylactic pharmacotherapy.

• Prophylactic combination therapy (pharmacotherapy and psychological intervention/psychosocial support).

• Doctor-patient cooperation expressed as the degree of adherence to the internationally recommended treatment guidelines.

It was recommended that the current organisation of outpatient treatment of patients with depressive or bipolar affective disorder should be supplemented with 5-10 specialised clinics in Denmark and that the clinics should:

1. be a supplement to the present decentralised treatment;

2. provide treatment of the highest professional standard;

3. offer both pharmacotherapy and psychological intervention;

4. regularly perform quality assurance and quality development of the interventions; and

5. provide education and perform research in diagnosis and treatment of affective disorder.

The staff in the outpatient mood disorder clinic at Rigshospitalet, Copenhagen University Hospital consists of full time specialists in psychiatry with specific clinical experience and knowledge on diagnosis and treatment of affective disorders as well as certified psychologists, nurses and a social worker with experience within affective disorders. The staff in the mood disorder clinic did not provide treatment to any of the patients in the standard treatment group.

### Intervention group

During the first year following establishment of the clinic a detailed intervention program including manuals for psychological group interventions (psychoeducation and cognitive behavioural therapy) was developed, tested, and revised in a pilot phase with inclusion of approximately 30 patients. The final combined pharmacological and non-pharmacological intervention program was as following. Separate intervention programs are provided for patients with bipolar disorder and patients for unipolar disorder lasting two years for patients with bipolar disorder (trial I) and one year for patients with unipolar disorder (trial II)(a minor proportion of patients who did not achieve remission during these periods were offered further individual treatment). According to the protocol, the physician evaluates all patients in the clinic less than two weeks after discharge from the local psychiatric ward. Although most patients improve during hospitalisation for affective disorders it is well known that they do still suffer from affective symptoms at discharge from hospitals in the Copenhagen area [64]. Prior course of illness and effect of treatment is carefully recorded and diagnosis and treatment plans are re-evaluated and current pharmacological treatment adjusted in accordance with clinical status and the national [65,66] and international guidelines [67-71]. Patients with a unipolar depressive disorder were offered acute and prophylactic treatment with ssri's/dual action drugs depending on individual effects and side effects. In case of poor response, switch was made to nortriptyline and if necessary, subsequently in combination with lithium. The main mood stabilisers for bipolar disorder were lithium, lamotrigine and valproate that for some patients were combined with atypical antipsychotics (mainly olanzapine, quetiapine, aripiprazole) or antidepressants for shorter time periods. Decisions on patient's individual pharmacotherapy were made by the individual physician in accordance with the other specialists in psychiatry and other providers at weekly staff conferences. Prescription of medication and adherence to medication will be characterised using the national medication register of all medication purchased at pharmacies in Denmark. Subsequently, the physician follows the patients with regular appointments depending on their clinical status and needs. In addition, patients participate in three different sequential group sessions weekly. All sessions are carried out in accordance with the manuals although individualised according to characteristics and needs of patients in the group. The first group is a settling-in group for patients just discharged from hospitalisation and with focus on the current clinical status, beliefs, and experiences in relation to the recent hospitalisation. Patients stay in this group until they are clinically stable and in at least partly remitted from affective symptoms (Hamilton Depression Score-17 items <14 and Young Rating Mania Scale <14), i.e., typically for some months up to half a year. When stable, the patients join a second and intermediary group consisting of either group psychoeducation or cognitive behavioural therapy. The type of group therapy is decided by the clinician and the patient in collaboration. The group sessions consist of 11/2 hours intervention every week for 12 consecutive weeks. In both groups, focus is on knowledge and acceptance of suffering from an affective disorder (bipolar or unipolar), identifying affective symptoms from normal reactions, personal identity in relation to suffering from an affective disorder, risk situations, stress management, the need for sustained pharmacological maintenance treatment, adverse events due to treatment, and identification of individual prior early warning signs of upcoming affective episodes. In addition, the cognitive behavioural therapy group sessions focus on inter-individual conflicts and cognitive distortions in identity and behaviour. Finally, the patients join a 3-6 months training discharge group that is a preparation for re-referral to the initially referring physician with the aim of identifying individual early warning signals *prospectively *in practice and training of how to change upcoming personal conflicts and cognitive distortions.

Six to eight patients and two therapists (psychiatrist, psychologist, or nurse) participate in each group. In the cognitive behavioural groups, at least one therapist has a formal education in cognitive behavioural therapy. Adherence to group treatment programmes is recorded. Parallel to these sessions, relatives to patients with bipolar disorder were offered a manual based psychoeducative group course consisting of 2-hours sessions weekly for six weeks.

The physician directs and co-ordinates treatments and makes decisions on discharge, in accordance with other health-care providers.

### Control group

The control group of patients were offered standard outpatient care consisting of the standard mental health service routines in The Capital Region of Denmark which is rather similar across the geographical catchments areas associated with the seven wards, i.e., treatment at the general practitioner, a private psychiatrist, or at the community mental health centre. Participation in the trials had no influence on the treatment offered to these patients. Compared with the intervention in the mood disorder clinic, psychopharmacological treatment is likely to be more based on the preferences of the individual medical physician than on national and international guidelines. Prescription of medication will be characterised using the national medication register of all medication purchased at pharmacies in Denmark. Psychosocial treatment elements like psychoeducation and cognitive behavioural therapy, and contact with family is in general provided infrequently and in a less intensive, non-systematic way and only for a minority of the control patients.

### Outcome assessments

Patients in the experimental intervention group and in the control group had been hospitalised to the same psychiatric departments prior to randomisation and would be readmitted to the same department if re-hospitalisation would be needed following randomisation.

The primary outcome is time from randomisation to first re-admission to a psychiatric ward with an affective episode. Data on re-hospitalisation will be obtained one, two, and five years following randomisation from the nation-wide Danish Psychiatric Central Register that contains data on all inpatients and outpatients contacts to all psychiatric hospital based services in Denmark [72]. Since 1 January 1994 the ICD-10 has been in use in the register [73].

The secondary outcome measures are 1) the development of a depressive or manic/mixed episode of at least moderate severity - together and separately, one and two years after randomisation and 2) adherence to maintenance antidepressant and mood stabilizing treatments one and two years after randomisation. These outcomes were assessed using questionnaires that were send to all participants one and two years following randomisation: the Major Depression Inventory (MDI) [74-76] and the Mood Disorder Questionnaire (MDQ) [77,78]. A depressive episode (of at least moderate severity) is defined as the presence of two or three depressive core symptoms and four to seven accompanying symptoms on the MDI. A manic or mixed episode is defined as a score of seven or more on the MDQ. The Antidepressant Compliance Questionnaire and the Mood stabilizer Compliance Questionnaire were used for measuring compliance with treatment modified after Demyttenaere [79,80].

The tertiary outcome are satisfaction with the intervention one and two years after randomisation estimated by the WHO (Five) well-being index [81,82] and the Verona Satisfaction Scale-Affective Disorder (VSS-A) [83]. Death due to suicide will be identified using register data from the Danish Medical Register on Vital Statistics [84].

Psychiatric outpatient contact and use of medication will be analysed for the intervention and control groups using register based data. Thus, we will have complete (register based) data on re-hospitalisation, medication and suicide whereas questionnaire based data will be missing for some patients who drop out of the trials.

### Sample size calculation

Anticipating a hazard ratio (HR) of 0.65 in the comparison of the intervention group with the control group on the primary outcome, a two-sided risk of type 1 error, α, of 0.05, a type 2 error risk, β, of 20%, and equal group size, the sample size (N) for trial I was calculated to N = 176 under the further assumption of a median time to re-hospitalisation of approximately 6 months in the control group, an inclusion period on 36 months, and a follow up period of 12 months. The sample size in trial II was based on similar assumptions (see Figure 1). However, patients with unipolar depressive disorder are more prevalent than patients with mania or bipolar disorder. Hence, we expected to be able to randomise more patients with unipolar depressive disorder. If we finally accrued a higher sample size in trial II compared to trial I, then the power for detection of a HR of 0.65 would become higher than 80%. The required sample sizes were calculated with the prospect of using a log rank test-statistic to test the null-hypothesis of no difference in time from randomisation to the primary outcome of re-admission to psychiatric hospital.

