**Figure 1 F1:**
[figure not shown]
**Anticipated statistical power estimations in Trials I and II**. The anticipated power in the trials on the x-axis as a function of the sample size of the trials on the y-axis based on α = 0.05 and an anticipated hazard ratio of 0.65 and 6 month median time from randomisation to re-admission to hospital in the control group, 48 month inclusion period, and at least a 12 month follow up of all patients.

The assumption of time to re-hospitalisation was based on national hospital data showing that half of all patients hospitalised with a diagnosis of depression or mania/bipolar disorder are re-hospitalised within a few months [85]. The assumption that the proportion of re-admission would be 35% decreased in the intervention group compared with the intervention group was based on findings of the effect of psychoeducation in bipolar disorder [86] and further on presumptions of positive effects of the early contact to patients during the vulnerable period following hospital discharge (less than two weeks) and a low drop out in the intervention group as experienced during the pilot phase of the trials.

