## Results

### Current trial status

Recruitment of bipolar patients was somewhat slower than expected, so the recruitment period had to be extended one year further than the originally planned three-year inclusion period for both patient groups. Thus, patient enrolment started in December 2005 and closed in December 2009, resulting in enrolment and randomisation of a total of 426 participants, 158 with bipolar disorder and 268 with unipolar disorder. Accordingly, we did not reach the planned number of 176 patients with bipolar affective disorder. Among unipolar patients, 63.1% were women and the median age was 38.6 years (quartiles: 31.1 to 53.4). Among bipolar patients, 54.4% were women and the median age was 35.6 years (quartiles: 27.7 to 47.1).

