### Power calculations for trials I and II

In the bipolar disorder trial I, the number of 158 recruited patients results in a power of 76% (power = 1-β) for the detection or rejection of a HR of 0.65. In the unipolar disorder trial II, the number of 268 recruited patients results in a power of 93% for the detection or rejection of a HR of 0.65. The power in trial I would be 60% and the power in trial II 82% to detect or reject a HR of 0.70. The power in trial I would be 42% and the power in trial II 63% to detect or reject a HR of 0.75. The statistical power in the two trials is calculated with the prospect of using a log rank test-statistic to test the null-hypothesis of no difference in time from randomisation to the primary outcome.

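### Trial I's sample size of 176 does not follow from its printed inputs: they require about 188 patients, and 176 gives about 77% power

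*Protocol article*

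**What the plan says.** Under Sample size calculation the article lists every input to the calculation:

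- The effect: "Anticipating a hazard ratio (HR) of 0.65 in the comparison of the intervention group with the control group on the primary outcome".
- The error rates: "a two-sided risk of type 1 error, α, of 0.05" and "a type 2 error risk, β, of 20%, and equal group size".
- A control median of about 6 months, 36 months' inclusion, 12 months' follow-up, and a log-rank test.

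The result is that "the sample size (N) for trial I was calculated to N = 176".

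The direction of the effect is not in doubt. The text after the Figure 1 caption begins "The assumption that the proportion of re-admission would be 35% decreased in the intervention group". The caption itself keeps the hazard ratio and the median but uses a different recruitment period: "48 month inclusion period, and at least a 12 month follow up of all patients".

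The figure of 176 is used again under Current trial status ("we did not reach the planned number of 176 patients"). The section on power for trials I and II then says "the number of 158 recruited patients results in a power of 76" per cent at a hazard ratio of 0.65. It gives five further powers and names no inclusion or follow-up period.

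**The concern.** The section prints a complete set of inputs and an output, so a reader can check one against the other, and they disagree. The figure is too small by an amount that rounding does not explain.

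Three things depend on it. Trial I's recruitment shortfall is measured against 176: 176 − 158 = 18 patients, where the printed inputs imply 188 − 158 = 30. The stated target would itself have given less than 80% power. And the powers for the recruited numbers are offered as grounds for detecting or rejecting given hazard ratios, so a null result in trial I would be read against them.

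**Working it through.** **Inputs.** From Sample size calculation: hazard ratio (HR) 0.65, two-sided α 0.05, power 80%, equal groups, control median 6 months, inclusion A = 36 months, follow-up F = 12 months after the last inclusion. From the Figure 1 caption: A = 48, F = 12. No drop-out is assumed, because Outcome assessments says that register data on re-hospitalisation will be complete. Exponential times and uniform accrual are my assumptions.

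**Events (Schoenfeld).** D = 4(1.960 + 0.842)² / (ln 0.65)² = 169.2, so 169 to 170.

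**Event probability.** With hazard λ, p = 1 − [exp(−λF) − exp(−λ(A + F))] / (λA). The control hazard is ln 2 / 6 = 0.1155 per month and the intervention hazard is 0.65 × 0.1155 = 0.0751, a median of 6 / 0.65 = 9.2 months.

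**Required N on the printed inputs.**

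| Inclusion + follow-up (months) | p control | p intervention | Mean | N = 169.2 / mean | Power at 176 |
|---|---|---|---|---|---|
| 36 + 12 | 0.941 | 0.860 | 0.900 | 187.9, so 188 | 77.4% |
| 48 + 12 | 0.955 | 0.890 | 0.923 | 183.3, so 184 | 78.4% |

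Other standard formulas move further from 176: Freedman and the exponential rate-difference method both give 194 at 36 + 12. Reading the 12 months as a fixed period for every patient gives 252. A log-rank simulation (20,000 runs) at 36 + 12 gave 76.5% power for 176 patients and 80.0% for 188.

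**Attempts to reproduce 176.** Each route below changes one printed input (the fourth drops censoring). Powers are for HR 0.65 / 0.70 / 0.75.

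| Change | N | Trial I, 158 patients | Trial II, 268 patients |
|---|---|---|---|
| Stated in the article | 176 | 76 / 60 / 42 | 93 / 82 / 63 |
| HR inverted (intervention median 6 × 0.65 = 3.9 months), 36 + 12 | 176.0 | 75.6 / 59.3 / 42.4 | 93.3 / 81.6 / 63.4 |
| Correct direction, 36 + 24 | 175.5 | 75.8 / 59.8 / 43.0 | 93.3 / 82.0 / 64.2 |
| Correct direction, control median 4 months, 36 + 12 | 176.5 | 75.5 / 59.5 / 42.8 | 93.2 / 81.8 / 63.9 |
| Freedman, every patient re-admitted | 175 | 76.0 / 60.2 / 43.5 | 93.5 / 82.4 / 64.8 |

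The inversion is the closest: no power is more than 0.7 points from the stated value. The second and third routes stay within about 1.2 points, and the fourth within 2.

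**Powers for the recruited numbers, correct direction, control median 6 months.**

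| Inclusion + follow-up (months) | Trial I | Trial II |
|---|---|---|
| 36 + 12 | 72.9 / 57.0 / 40.9 | 91.7 / 79.5 / 61.6 |
| 48 + 12 | 73.9 / 58.0 / 41.6 | 92.3 / 80.4 / 62.5 |
| 48 + 24 | 76.1 / 60.1 / 43.2 | 93.5 / 82.2 / 64.5 |

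At 48 + 12 the stated values are higher by 2.1, 2.0 and 0.4 points in trial I and by 0.7, 1.6 and 0.5 in trial II. At 48 + 24 all six are met.

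**The case against.** A reader might infer that the authors must have entered the hazard ratio backwards, since that one change recovers 176 and all six powers. The inference is reasonable but not established. The article names neither formula nor software, and other single changes with the effect in the right direction fit nearly as well. What this objection does not do is rescue the printed text: 24 months' minimum follow-up contradicts the stated 12, a 4-month control median contradicts the stated 6, and a calculation without censoring ignores the stated periods.

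A reader might also infer that every stated power is too high. That does not hold either. The section on power gives no inclusion or follow-up period, the Figure 1 caption describes its 12 months as a minimum, and Outcome assessments plans register readouts at one, two and five years. With two years' minimum follow-up the stated powers are reached. The Figure 1 curve is not available here, so its values cannot be called wrong.

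Finally, the 6-month median is only approximate. With 5 months and 48 + 12, N is 179 and trial I's power is 75.0%, so the gap is of the order of the uncertainty in that input. This limits how much the error matters. It does not make the printed inputs yield 176.

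**Conclusion.** The point stands for the sample size. On the inputs printed beside it, 176 should be about 188, an increase of 12 / 176 = 6.8%, and 176 patients have about 77% power. On Figure 1's 48-month inclusion the corresponding figures are about 184 and 78%. The two periods should not be mixed: 188 goes with about 73% power for the 158 patients recruited to trial I, and 184 with about 74%.

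An inverted hazard ratio is the best explanation but remains an inference. The stated powers are at most about 2 points too favourable on 48 + 12 months, and are not shown to be wrong if a longer follow-up was meant.

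These results assume exponential times, uniform accrual and no loss to follow-up. Severity is minor to moderate: recruitment has closed, the article already reports the shortfall and a power below 80% for trial I, and the planned analyses are unaffected.

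**What to change.** Check the direction of the hazard ratio in the calculation and name the formula used. Then do one of two things in the sample size section:

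- keep the inputs and restate the required N as 188 for 36 + 12 months, or about 184 if 48 + 12 is adopted; or
- keep 176 and correct the input that was actually used.

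State one inclusion period and one minimum follow-up for both the power section and Figure 1, and give the powers on that basis. If it is 48 + 12, they are about 74 / 58 / 42% for trial I and 92 / 80 / 62 to 63% for trial II at hazard ratios of 0.65 / 0.70 / 0.75. Adjust the shortfall under Current trial status to the corrected target.

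The change is to wording only, with no further enrolment. The cost is that the stated figures become slightly less favourable.
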